## **7.2.4 Evaluation of uterine MR and uterine histology**

Pilot and Main Study

Both the endometrial and myometrial/leiomyoma compartments of the uterus will examined in response to medication.

Hysterectomy specimens will be examined by a sub-specialist gynaecological pathologist or a nominated deputy. After removal of the uterus in the operating theatre, an endometrial Pipelle biopsy will be taken in theatre and placed in RNA later. The uterus will then be transferred without delay to the pathology laboratory. The uterus will be ‘sliced’ in the plane in which it will be scanned. Biopsies will be taken of myometrium and leiomyoma and placed in RNA later. Formalin will then be instilled to fix the endometrium, the cervix will be plugged, the uterus will be securely packaged and escorted by member of research team to the MR imaging facility for ex vivo examination as described above. Thereafter the uterus will be escorted back to the laboratory for the whole specimen to be placed in formalin and fixed overnight. It will subsequently be sliced in the same plane as the MRI images, photographed and histology carried out.

**7.2.5 Blood Sampling**

Pilot Group A

Blood samples will be taken on 3 occasions -

At Screening, Day 28+/- 3 days (to assess Urea and Electrolytes (U&E's), Full Blood Count (FBC), and Liver Function Tests (LFT's). and on the day of Hysterectomy (Visit 3) to assess as per previous visits plus Oestradiol (E), Progesterone(P), Luteinising Hormone (LH) and Follicle Stimulating Hormone (FSH)

Pilot Group B

Blood samples will be taken on 2 occasions -

At Screening (to assess Urea and Electrolytes (U&E's), Full Blood Count (FBC), and Liver Function Tests (LFT's) and on the day of Hysterectomy (Visit 2) to assess as per previous visits plus Oestradiol (E), Progesterone(P), Luteinising Hormone (LH) and Follicle Stimulating Hormone (FSH)

Pilot Group C

Blood samples will be taken on 2 occasions -

At Screening (to assess Urea and Electrolytes (U&E's), Full Blood Count (FBC), and Liver Function Tests (LFT's) and on the day of Hysterectomy (Visit 2) to assess as per previous visits plus Oestradiol (E), Progesterone(P), Luteinising Hormone (LH) and Follicle Stimulating Hormone (FSH)

Main Study

A 10ml blood sample will be obtained on 11 occasions (Group 2) and 10 occasions (Groups 1 & 3) to obtain an estimate of Oestradiol (E), Progesterone(P), Luteinising Hormone (LH) and Follicle Stimulating Hormone (FSH). Urea and Electrolytes (U&E's), Full Blood Count (FBC), and Liver Function Tests (LFT's) will be checked at screening, Day 28+/- 3 days (Visit 3) and on the day of Hysterectomy (Visit 5).

- - 1. **Urine Collection**

Main Study only

5mls urine samples collected twice weekly to measure sex steroid hormone metabolites. Up to 30 samples in total. Instructions will be given to participants. Patient is asked at each point of contact if collection is being completed and if more sample bottles are required. A small drop if glycerol is put into the sample bottles to help with the freezing process. This has no effect on the analysis of the sample.

**7.2.7 Menstrual Recording**

Main Study Only

A daily record of menstrual bleeding maintained by the participant. This is given to patients at Visit 1 and collected on day of hysterectomy. Patients are asked at each point of contact if chart is being completed.

# **DATA COLLECTION**

CRFs have been created by research staff. Clinical research assistant, nurses or Clinical Research Fellow will collect data on CRFs. Data will be collected at each point of contact with participant.

# **STATISTICS AND DATA ANALYSIS**

## **9.1 SAMPLE SIZE CALCULATION**

No sample size required for pilot group.

Sample size calculations for this sort of study are very difficult. This is a hypothesis generating study, and findings will need to be confirmed in a separate larger study. A sample size of 10 patients in each group will give an 80% power, at a significance level of 5%, to detect a difference in the change in volume of 160cm cubed (s.d of change in volume = 120cm cubed) between a treated group and the control group. This calculation does not take multiple comparisons into account.

In terms of agreement 30 subjects would allow us to estimate limits of agreement +/- 0.6 standard deviations of the difference between measurements using Bland-Altman methods.

## **9.2 PROPOSED ANALYSES**

We will perform per protocol and Intention to Treat (ITT) analyses. Standard statistical analysis packages will be used. Given the limited sample size, only descriptive statistics will be used. This is however a hypothesis generating study and the statistical analyses performed will be within this context.

Missing data will be kept to a minimum, and where possible will be collected from patients regardless of whether they have been compliant with their allocated treatment.  Statistical analyses will involve sensitivity analyses to assess the effect of missing data.  We will collect reasons for missing data.

The randomisation scheme will be drawn up by an independent statistician, and the allocated treatment codes will be put into sealed consecutively numbered opaque envelopes.  When a patient is randomised into the study, she will receive the treatment indicated in the next available envelope.

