# **STUDY OBJECTIVES**

## **2.1 OBJECTIVES**

### **2.1.1 Primary Objective**

##### To establish the feasibility and reproducibility of novel MR imaging techniques in the evaluation of treatment response in women with uterine leiomyomas (fibroids).

### **2.1.2 Secondary Objectives**

To provide mechanistic information on whether the reduction in blood flow of uterine/fibroid vasculature in shrinkage fibroids is dependent upon subjects being hypoestrogenic.

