### **2.2.2 Secondary Endpoints**

1. Uterine vascular perfusion

1. Vasculature and extracellular matrix (ECM content of fibroids)

3. Whether (a) reduction of blood flow of uterine and fibroid vasculature and (b) shrinkage of fibroid depends upon subject being hypoestrogenic.

NB. The study aims to establish feasibility and reproduce ability of novel MR imaging techniques in the evaluation of treatment response in women with uterine fibroids. Hence there is not an efficacy measurement required for any of the drug treatment options.

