**Primary analyses will be:**
(1) the comparison of the pre-hysterectomy uterine volume between the treated and control groups using t-test or a non-parametric equivalent as appropriate.:

(2) Bland-Altman analyses comparing the pre-hysterectomy MR with USS.

**Secondary analyses**: We will perform similar analyses for uterine vascular perfusion. A variety of other exploratory analyses will be performed including examining changes over time, and quality of images. Data will also be considered in the context of the patient’s hormone profile over the time of the study (taken from blood and urine samples).

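### Section 9.2 limits the analysis to descriptive statistics yet makes a two-group test its primary analysis (1), and the 80% power in 9.1 is for a different quantity from the one tested

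*Protocol*

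**What the plan says.** Section 9.2 of the protocol opens by restricting the method: "Given the limited sample size, only descriptive statistics will be used". It adds that the study is hypothesis generating and that its analyses belong in that context.

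Further on, 9.2 lists two primary analyses. The first is "the comparison of the pre-hysterectomy uterine volume between the treated and control groups using t-test or a non-parametric equivalent as appropriate". The second is "Bland-Altman analyses comparing the pre-hysterectomy MR with USS".

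Section 9.1 gives two justifications for the main study's size:

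- On the group comparison: "A sample size of 10 patients in each group will give an 80% power", at 5% significance, for a difference of 160 cm³ in the change in volume between a treated group and control, with an SD of change of 120 cm³. It says openly that multiple comparisons are not allowed for.
- On agreement: 30 women would fix the limits of agreement to within about 0.6 SD of the between-method differences.

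**The concern.** A t-test, or its rank-based counterpart, is an inferential procedure. A plan that permits descriptive statistics only and also names such a test as a primary analysis gives two incompatible instructions, in the same section. The conflict reaches 9.1 as well, because the group size is defended by the power of a test that 9.2 says will not be used.

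There is a second mismatch. Section 9.1 plans for the change in volume, while primary analysis (1) compares the volume reached before surgery, with no reference to baseline. These are different outcomes with different SDs. A report that ran the test as written and cited 80% power would attach the figure to an analysis it was not computed for.

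At stake are a clear instruction to the analyst and an honest account of what 10 women per group can show. No patient procedure is affected.

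**Working it through.** **1. The statements side by side.**

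| Place | Instruction |
| --- | --- |
| 9.2, opening paragraph | Descriptive statistics only |
| 9.2, primary analysis (1) | t-test or non-parametric test, treated versus control, on pre-hysterectomy volume |
| 9.1 | 10 per group, 80% power at 5%, on change in volume |

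Rows 1 and 2 cannot both be carried out. Row 3 presupposes a test, but of a different variable from row 2.

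**2. Reproducing the 80%.** Inputs from 9.1: difference 160 cm³, SD of change 120 cm³, n = 10 per group, 5% significance. The number of sides is not stated; two-sided is assumed.

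- Standardised difference: d = 160/120 = 1.333.
- Noncentrality: d × √(n/2) = 1.333 × √5 = 2.98, on 18 degrees of freedom.
- Power from the noncentral t distribution: 80.5%. The required n is 9.9 per group.

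The alternatives fit less well: the normal approximation gives 84.6%, and a one-sided t-test gives 88.9%. The published figure is therefore the power of a two-sided, 10-versus-10 t-test on change, and it is arithmetically correct.

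**3. Does it carry over to the test in 9.2?** That would need the SD of pre-hysterectomy volume, which the protocol does not give. Holding the difference at 160 cm³ and varying this SD (assumed values):

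| SD of pre-hysterectomy volume (cm³) | Power, 10 versus 10, two-sided 5% | Implied baseline-to-final correlation |
| --- | --- | --- |
| 120 | 80.5% | 0.50 |
| 150 | 62% | 0.68 |
| 200 | 40% | 0.82 |
| 300 | 20% | 0.92 |

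The last column assumes equal SDs at Visit 1 and before surgery, so that SD of change = SD × √(2(1 − r)) and r = 1 − 120²/(2 × SD²). For SD 200, for example, r = 1 − 14,400/80,000 = 0.82. Under that assumption the 80% carries over only when r is 0.5. Power is lower when the two volumes are more strongly correlated and higher when they are less so.

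**4. The agreement figure.** The 95% half-width for a limit of agreement is about 1.96 × √(3/n) = 1.96 × √(3/30) = 0.62 SD, which matches the stated 0.6. This part of 9.1 supports the Bland-Altman analysis and needs no correction.

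**The case against.** The best defence is that the protocol twice calls itself hypothesis generating, says its findings need confirmation in a larger study, and admits that multiplicity is ignored. On this view, descriptive is loose wording for not confirmatory, and detail on the contrast can wait for the statistical analysis plan. The point about intent is fair. It does not remove the conflict: the label governs how a result is read, and does not turn a t-test into a descriptive summary. Because both statements stand in the protocol, an analysis plan that follows one departs from the other.

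Several stronger readings are tempting, but the documents do not support them:

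- A reader might infer that the note under 2.2.2, "Hence there is not an efficacy measurement required for any of the drug treatment options", rules out the comparison. It says only that such a measurement is not required. The primary objective concerns MR in evaluating treatment response, and the primary endpoint concerns changes in uterus and fibroid volume, so a treated-versus-untreated comparison of volume is compatible with both.
- A reader might infer that the drug comparison is the sole primary analysis, or that the headline result would be picked once the data are in. Section 9.2 names two primary analyses in advance, and the Bland-Altman analysis has its own precision statement.
- A reader might infer undisclosed multiplicity. Section 9.1 discloses it, and its wording describes 10 women against 10. An adjusted significance level is proposed nowhere, so its absence is not an error in a declared hypothesis-generating study.

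**Conclusion.** The point holds as a contradiction within 9.2 and a mismatch between 9.1 and 9.2. The contradiction is textual and rests on no assumption. The 80% is correct for what it describes, a two-sided comparison of change in one treated arm against control. It does not describe the comparison of pre-hysterectomy volume that 9.2 names. How far the power of that test departs from 80% cannot be settled from the protocol. The range of 62% to 20% depends on assumed SDs of 150 to 300 cm³ and on keeping the difference at 160 cm³.

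A reader might also conclude that primary analysis (1) should be demoted, or that the study's conclusion should rest on repeatability. Demotion is a matter of preference that the text does not compel. Repeatability cannot be estimated from the planned imaging records: section 3.1.2 provides a single record of each measurement at each time-point, so the planned Bland-Altman analysis shows agreement between MR and ultrasound and not the repeatability of either. This is worth correcting, but it does not undermine the design.

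**What to change.** - **Section 9.2, opening paragraph:** delete the sentence confining the analysis to descriptive statistics. Keep the statement that the study is hypothesis generating.
- **Section 9.2, primary analysis (1):** define it as each treated arm minus control, either adjusted for Visit 1 volume or on change from Visit 1, reported with a 95% confidence interval and read as hypothesis generating. This brings the analysis into line with the change-in-volume basis of 9.1.
- **Section 9.1:** say that the 80% applies to each arm-versus-control comparison of change in volume and is not adjusted for there being two such comparisons.
- **Section 9.2, primary analysis (2):** keep the MR-versus-ultrasound Bland-Altman analysis as the primary analysis that addresses the imaging objective, and describe it as agreement, not repeatability.

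The cost is a protocol amendment to 9.1 and 9.2. The form of primary analysis (1) changes, so this is slightly more than an editorial correction. Visit 1 imaging is already scheduled before randomisation, so no extra visit, scan or participant is needed.

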**Primary analyses will be:**
(1) the comparison of the pre-hysterectomy uterine volume between the treated and control groups using t-test or a non-parametric equivalent as appropriate.:

(2) Bland-Altman analyses comparing the pre-hysterectomy MR with USS.

**Secondary analyses**: We will perform similar analyses for uterine vascular perfusion. A variety of other exploratory analyses will be performed including examining changes over time, and quality of images. Data will also be considered in the context of the patient’s hormone profile over the time of the study (taken from blood and urine samples).

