##### Clinical MR imaging will be performed. Patients will be examined on four occasions:

##### (1) before commencing GnRH agonist, GnRH antagonist therapy (visit 1);

##### (2) after 14 days+/- 3 days (visit 2);

##### (3) after 28 days +/- 3 days (visit 3);

##### (4) within 10 days prior to hysterectomy(visit 4)

Pre- and post GnRH agonist / GnRH antagonist treatment and control subjects will undergo breath-hold fast-spin-echo T2-weighted imaging acquired in planes oblique to the uterus, magnetization transfer, contrast-enhanced T1-volume scans and dynamic contrast imaging using a phased array torso coil on MR scanner.

Dynamic contrast imaging will use T1-weighted SPGR scans acquired at a number of time points after injection of gadolinium, e.g.  = 0, 30, 60, 90, 120 180, 240 and 300 seconds (Have practical limits in that patients usually become restless after about 30-40 minutes in MRI). Development work will be required to determine the optimum number and temporal resolution for this imaging to allow analysis of fibroid perfusion and permeability. Subjects will be carefully positioned so that the scan locations are as close as possible between pre- and post-treatment examinations. The use of image registration methods, such as FLIRT (www.fmrib.ox.ac.uk/fsl), to allow further fine alignment of imaging data will be investigated.

Uterus and enhancing and non-enhancing fibroid volumes pre- and post treatment will be determined from the T2- and T1-weighted structural scans using ANALYZE (Mayo Foundation, Rochester, MN, USA). Reduction in uterus and fibroid volumes will be determined as 100  (Volpre – Volpost)/Volpre.

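### The 80% power in Section 9.1 is for change in volume, but primary analysis (1) in Section 9.2 tests the pre-hysterectomy volume alone, so the stated power does not apply to the test as written

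*Protocol*

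**What the plan says.** Section 9.1 sets 10 women per group for 80% power, "at a significance level of 5" per cent, "to detect a difference in the change in volume of 160cm cubed", with "s.d of change in volume = 120cm cubed". The contrast is "between a treated group and the control group". It does not say whether the volume is that of the uterus or of the fibroid, or whether the test is two-sided.

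Section 9.2 lists as primary analysis (1) "the comparison of the pre-hysterectomy uterine volume between the treated and control groups using t-test or a non-parametric equivalent as appropriate". It neither subtracts nor adjusts for the Visit 1 volume. Change over time appears only later in 9.2, among the exploratory analyses.

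Three other places bear on the point:

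- Section 2.2.1 words the primary endpoint as feasibility and reproducibility of MR imaging in quantifying changes in uterus and fibroid volume.
- Section 3.1.2 and the Appendix 4 charts place the Visit 1 MRI before randomisation in all three main-study groups.
- Section 9.2 also says that, with so few patients, the statistics will be descriptive only, and Section 9.1 calls the study hypothesis generating.

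**The concern.** The quantity that was powered is not the quantity tested. Change within a woman removes her starting uterine size; a single post-treatment volume keeps it. If starting size varies widely between women and persists to Visit 4, a comparison of Visit 4 volumes is noisier than a comparison of changes. Any chance difference between arms in starting volume also passes into the result.

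With 10 women per arm, that could hide a real shrinkage or look like one. A reader of the final report would take the 80% in Section 9.1 as the sensitivity of the first-listed primary analysis, and the protocol gives no basis for that.

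**Working it through.** **Inputs from the protocol (Section 9.1).** n = 10 per group, difference 160 cm³, SD of change 120 cm³, 5% level. Two-sided testing is an assumption; it is the version that matches the stated figure.

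**Step 1: reproduce the stated power.** Standardised difference d = 160/120 = 1.333. The two-sample t-test (noncentral t, 18 df) gives 80.5%, and 80% power needs 9.89, so 10, per group. Section 9.1 is correct for its own inputs.

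**Step 2: move to the test in Section 9.2.** The SD of raw volume, σ, is not given. Assume the same σ at Visits 1 and 4 and a pre-post correlation r. Then

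SD of change = σ√(2(1 − r)), so σ = 120/√(2(1 − r)).

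Example at r = 0.8: σ = 120/√0.4 = 189.7 cm³, d = 160/189.7 = 0.843, power 43%.

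| r (assumed) | Raw SD (cm³) | Power, Visit 4 volume only, 10 v 10 |
|---|---|---|
| 0.3 | 101 | 92% |
| 0.5 | 120 | 80.5% |
| 0.6 | 134 | 71% |
| 0.7 | 155 | 59% |
| 0.8 | 190 | 43% |
| 0.9 | 268 | 24% |
| 0.95 | 379 | 14.5% |

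**Step 3: break-even.** With 10 per group, 80% power needs d = 1.325, so a raw SD of at most 160/1.325 = 121 cm³, which corresponds to r of about 0.51.

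**Step 4: is a raw SD of 121 cm³ plausible?** Section 1.1 cites average shrinkage of 20–50%. If 160 cm³ stands for that shrinkage (an assumption), mean volume lies between 160/0.50 = 320 and 160/0.20 = 800 cm³. A raw SD of 121 cm³ is then a between-woman coefficient of variation of at most 121/320 = 38% down to 121/800 = 15%. The protocol has no figure to compare with this.

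**Step 5: chance imbalance.** The standard error of the difference in mean starting volume between two arms of 10 is σ√(2/10). At r = 0.8 this is 189.7 × 0.447 = 85 cm³, about half of the 160 cm³ target.

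**Step 6: the alternatives.** A t-test of change from Visit 1 to Visit 4 has the 80.5% of Step 1. For Visit 4 volume adjusted for Visit 1 volume (ANCOVA, 17 residual df), simulation with random baselines, 10 v 10, gives about 84%, 82%, 80% and 79% at r = 0.7, 0.8, 0.9 and 0.95.

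**The case against.** The strongest reply is that this test does not decide the trial. The objective is feasibility and reproducibility of imaging, Section 2.2.2 says that no efficacy measurement of the drugs is needed, and Section 9.2 promises only descriptive statistics. This stands as a limit on severity. It does not remove the contradiction: Section 9.2 still names a t-test as primary, and Section 9.1 still attaches 80% power to the group size.

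Second, the loss rests on an assumed r. This also stands. At r of 0.5 or below, the written test has the stated power or more. If shrinkage is proportional to size, the SD at Visit 4 would be smaller in treated women and the table's SDs too high for that arm. If the wording of analysis (1) meant both treated groups pooled against control (20 v 10), power would be 84% at r = 0.6 and 73% at r = 0.7, but only 56% at 0.8. Section 9.1's wording favours single treated groups.

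A reader might infer more than the documents support in three ways:

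- That the primary test is shown to be badly underpowered. It is not, because the raw SD is unknown.
- That the percentage reduction in Section 7.2.3 ("Reduction in uterus and fibroid volumes will be determined as 100" times the relative fall) is a rival primary analysis. It defines a measurement; Section 9.2 does not name it as primary.
- That ANCOVA must do at least as well as Section 9.1, because its residual SD, σ√(1 − r²), never exceeds the SD of change. That overlooks the variance added by chance baseline imbalance, which brings power to about 79% at r = 0.95.

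**Conclusion.** The mismatch holds on the text alone: Section 9.1 powers change, and primary analysis (1) tests an unadjusted post-treatment volume. The 80% therefore cannot be quoted for that analysis.

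The size of the loss is conditional. With equal SDs at the two visits and 10 v 10, power falls below 80% once the raw SD exceeds about 121 cm³ (r above about 0.5). It would be 59% at r = 0.7 and 24% at r = 0.9. A correlation above 0.5 is what one would expect for the same uterus over 12 to 13 weeks, but nothing in the protocol establishes it. Because the study is hypothesis generating with a feasibility aim, the point should be fixed but does not undermine the trial.

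**What to change.** Reword primary analysis (1) in Section 9.2 in one of two ways, each treated arm against control, reported as a difference with a 95% confidence interval:

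- change in uterine volume from Visit 1 to Visit 4, which matches Section 9.1 directly, provided that the volume in 9.1 is confirmed as uterine; or
- Visit 4 uterine volume adjusted for Visit 1 volume by ANCOVA, with power of roughly 80% or better over most of the range examined.

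If the raw Visit 4 comparison is kept, withdraw the 80% claim or recompute it with a sourced SD of raw volume. In either case, reconcile the statement that only descriptive statistics will be used with the named test. A log-volume sensitivity analysis is optional.

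The cost is wording and at most one degree of freedom. No new data are needed, because the Visit 1 MRI is already scheduled before randomisation.

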## **2.2 ENDPOINTS**

### **2.2.1 Primary Endpoint**

Feasibility and reproducibility of use of structural, dynamic contrast and magnetization transfer (MTI) MR imaging to visualize and quantify changes in:

1. Uterus and fibroid volume

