**3.1.2 Measurements:**

Comparisons will be made between the following imaging modalities:

1. Sonographic assessment, colour Doppler imaging.
2. 1.5T MR imaging, including structural, dynamic contrast and magnetization transfer imaging.
3. Ex-vivo imaging with 7T MR scanner correlated with uterine histo-morphology.

For imaging exercises there will be one record per patient for each measurement at each time-point. The largest fibroid will be selected and total uterine volume measured.

It is not possible to have patients “blinded” to treatment option. It will be possible for the statistician, pathologists, radiologists, technicians and non clinical staff to be “blinded” to the treatment allocation, to the results of previous time-points, and to the results of other measures at the same time-point.

Following successful screening procedures all the participants will have a further 5 visits to the RIE.

On each of the visits 1 to 4 every participant will have a MRI, Ultrasound and Doppler. If Visit 1 falls within 28days of screening then the screening scan will remain valid. If this is anticipated then Dopplers will be carried out at screening.

Visit 1 will be carried out prior to randomisation (Within 28 days of Day 1)

Visit 2 at 14 days+/- 3 days following commencement of treatment

Visit 3 at 28 days+/- 3 days following commencement of treatment

Visit 4 Within 10 days prior to scheduled hysterectomy

Visit 5 Day of Hysterectomy and Ex-vivo imaging with 7T MR scanner of uterus

Blood samples will be taken on 3 occasions - at Screening, Day 28+/- 3 days (Visit 3)and on the day of Hysterectomy (Visit 5) to assess Urea and Electrolytes (U&E's), Full Blood Count (FBC), and Liver Function Tests (LFT's). These blood samples will be taken on scheduled study visits to the hospital.

A 10ml blood sample will be obtained on 11 occasions (Group 2) and 10 occasions (Groups 1 & 3) to obtain an estimate of Oestradiol (E), Progesterone(P), Luteinising Hormone (LH) and Follicle Stimulating Hormone (FSH). A small aliquot of blood will be stored in the freezer in reserve in case of any laboratory processing difficulties.

Some of these blood samples will be taken at the RIE when they coincide with Scheduled Study Visits. The participants will be given the option to have the rest of the blood samples taken in their own home if this is more convenient to them.

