### Subsequent scans (TVU / TAS) will be performed following start of medication at Visits 2, 3 and 4 (main study), Day 28+/- 3 days (Pilot Group A) and prior to hysterectomy (Pilot Groups A, B & C).and the same measurements will be carried out to record any changes from baseline.

## **7.2.2 Colour Doppler imaging**

To determine blood flow of the main uterine arteries colour Doppler imaging will be performed prior to the first study drug dose and repeated following start of medication at Visits 2, 3 and 4 (main study), Day 28+/- 3 days (Pilot Group A) and prior to hysterectomy (Pilot Groups A, B & C). Blood flow will be expressed using two impedance indices: the resistance index (RI) and the pulsatility index (PI). For each impedance index, the average of three measurements will be taken from the left and right arteries, respectively to enhance reproducibility.

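### Primary analysis (2) checks MR against ultrasound only on the final pre-hysterectomy scan, which cannot show whether the two methods agree on the change in volume that the primary endpoint concerns

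*Protocol*

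**What the plan says.** The primary objective (Protocol 2.1.1) is the "feasibility and reproducibility of novel MR imaging techniques in the evaluation of treatment response". The primary endpoint (2.2.1) is the feasibility and reproducibility of using "MR imaging to visualize and quantify changes in" uterine and fibroid volume.

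Three other places also work in terms of change:
- Section 7.2.3 defines the MR response as a percentage: "Reduction in uterus and fibroid volumes will be determined as 100" times the pre-to-post fall divided by the pre-treatment volume.
- The ultrasound section (7.2.1) repeats the scans so that "the same measurements will be carried out to record any changes from baseline".
- Section 9.1 bases the group size on a difference in the change in volume, 160 cm³ with an SD of change of 120 cm³.

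The second primary analysis in 9.2 is "Bland-Altman analyses comparing the pre-hysterectomy MR with USS". The line does not name the variable. Volume follows from the endpoint and from primary analysis (1). In the main study the pre-hysterectomy scan is "Visit 4 Within 10 days prior to scheduled hysterectomy". Section 9.1 gives the precision: "30 subjects would allow us to estimate limits of agreement +/- 0.6 standard deviations of the difference between measurements".

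On the data available, 3.1.2 states "On each of the visits 1 to 4 every participant will have a MRI, Ultrasound and Doppler". It then allows the screening ultrasound to stand if Visit 1 falls within 28 days of it, and Appendix 4 accordingly marks the Visit 1 ultrasound and Doppler entry as needed only if required.

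**The concern.** An endpoint about quantifying change is paired with an agreement analysis of a single level. Two methods can differ at every visit and still record the same fall, or coincide at the last visit and record different falls. Ultrasound volume is an ellipsoid estimate from three diameters (7.2.1), and MR volume is measured from the structural scans (7.2.3). A difference between them that depends on the shape of the uterus or fibroid is therefore plausible.

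At stake is what the reported limits of agreement can support. As written, they describe how closely the methods match on volume shortly before surgery. A reader assessing MR as a marker of response needs to know how closely they match on the measured response, and no analysis of that is specified.

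**Working it through.** **1. The plan's own figures.** The 95% half-width of a limit of agreement is about 1.96 × √(3/n) SDs of the differences. With n = 30 it is 1.96 × √(3/30) = 0.62, which matches the stated 0.6. Variants of the formula give 0.618 and, with a t quantile, 0.647. The group size also reproduces: a two-sample t-test with 10 per group, difference 160, SD 120 and two-sided 5% (sidedness assumed) has 80.5% power against the stated 80%.

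**2. Which scan is meant.** Section 3.1 (Pilot Group A) sets pre-hysterectomy against the scan before the agonist is given, and primary analysis (1) uses the same term for the volume compared between groups. The natural reading is the single final scan, Visit 4 in the main study.

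**3. Level against change.** With D = MR − USS,

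(MR₄ − MR₁) − (USS₄ − USS₁) = D₄ − D₁.

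Primary analysis (2) looks at D₄ only. D₁ does not enter.

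**4. Two illustrative women (invented values, cm³).**

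| | USS | MR | D₁ | D₄ | Fall, USS / MR | Percent fall, USS / MR |
|---|---|---|---|---|---|---|
| First | 500 → 400 | 600 → 400 | +100 | 0 | 100 / 200 | 20.0 / 33.3 |
| Second | 600 → 400 | 500 → 300 | −100 | −100 | 200 / 200 | 33.3 / 40.0 |

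The first woman shows no difference at Visit 4, but the methods differ on her response on both scales. The second shows a 100 cm³ difference at Visit 4 and none in absolute change, yet 6.7 points in percent reduction. The result for her depends on the scale.

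**5. The same in groups (assumed error SD 20 cm³ per method per visit).** The SD of D₄ is √(20² + 20²) = 28.3, so limits are ±1.96 × 28.3 = ±55. The SD of D₄ − D₁ is √(4 × 20²) = 40, so limits are ±78.
- MR reads 50 cm³ higher at every visit. Level: bias +50, limits −5 to 105. Change: bias 0, limits −78 to 78.
- Ultrasound reads 80 cm³ low at baseline in treated women and agrees at Visit 4. Level: bias 0, limits −55 to 55. Change in treated women: bias −80, limits −158 to −2.

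**6. Spread in general.** Assume D has the same SD s at both visits and correlation r between them. Then SD(D₄ − D₁) = s√(2(1 − r)).

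| r | SD for change | Half-width with 30 pairs (0.62 × SD) |
|---|---|---|
| 0 | 1.41s | 0.88s |
| 0.5 | 1.00s | 0.62s |
| 0.75 | 0.71s | 0.44s |
| 0.9 | 0.45s | 0.28s |

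Measured in SDs of its own differences, the precision is 0.62 for level and for change alike.

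**The case against.** Several points on the other side are sound.

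- **The question asked.** A reader might infer that the trial's stated question is whether MR and ultrasound measure the same response. Sections 2.1.1 and 2.2.1 do not name ultrasound. They ask about feasibility and reproducibility of MR, and the comparison between methods supports that. A change-based comparison would not itself measure MR reproducibility either.
- **A constant offset.** It is tempting to say the plan would count a constant offset as failure. It sets no acceptance limit, and a Bland-Altman analysis reports a common offset as mean bias, apart from the spread. Only offsets that vary between women widen the limits.
- **Cancellation.** An offset cancels in the change only if it is additive and stable and the change is in cm³. A proportional error would not cancel in cm³, and an additive one does not cancel on the percent scale of 7.2.3.
- **Baseline timing.** Baseline ultrasound may precede baseline MR by up to 28 days. Visit 4 has no such allowance, so level agreement there is the cleaner like-for-like comparison.
- **Context.** Section 9.2 describes hypothesis-generating work with descriptive statistics, and includes change over time among the exploratory analyses.

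These points limit how strongly the concern can be put, and they shape the remedy. They do not supply the missing comparison: the exploratory item does not mention agreement between methods. Nor is this a detail left open for an SAP, since the protocol itself fixes the primary agreement analysis on the single visit.

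**Conclusion.** The point holds in a limited form. The endpoint concerns change, the primary agreement analysis concerns level at one visit, and the second cannot establish or exclude agreement on the first. That follows from the identity in step 3 and needs no assumption about error sizes.

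The size in this trial is unknown. The multipliers from 1.41 to 0.45 rest on an assumed r between 0 and 0.9 and on equal SDs at the two visits, which is doubtful if treated uteri shrink. A reader might turn them into a claim that the planned limits are between 29% too narrow and 2.2 times too wide. The documents give neither r nor any SD of MR-ultrasound differences, so they do not support that as a finding about this trial, or say which direction applies.

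The arithmetic in 9.1 is correct. Agreement on level remains worth reporting. This is an inexpensive improvement to the plan and does not invalidate the existing analysis.

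**What to change.** In 9.2, extend primary analysis (2) along these lines: *Bland-Altman analysis of the change in volume from baseline to the pre-hysterectomy visit by MR against the change by ultrasound, for uterine and for fibroid volume, in women with both methods at both visits. Results are given as absolute change in cm³ and as percent reduction as defined in 7.2.3. Agreement on the pre-hysterectomy volume is reported alongside.*

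Add that the interval between the baseline MR and the baseline ultrasound will be reported, and that the change analysis will be repeated in women whose two baseline scans were done at the same visit.

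The cost is a few sentences and some derived variables, with no new scans or participants. Women without a baseline scan by either method leave the change analysis but stay in the level analysis. A gap between baseline scans can add apparent disagreement, which is the reason for the repeat analysis. That subset will be less precise: if 20 women qualified, for instance, the half-width would be 1.96 × √(3/20) = 0.76 SD instead of 0.62.
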